**1.3 Background.**

Treatment with bisphosphonate.

Multiple myeloma (MM) is a B-cell malignancy characterized by proliferation of monoclonal plasma cells in the bone marrow. One of the most devastating complications in MM is the severe loss of bone mass observed in the majority of the patients. Bone loss can either be observed as typical osteolytic lesions or as a more generalized osteopenia. At diagnosis, 79 percent of all patients present with abnormal findings on conventional radiography either caused by osteolytic lesions, fractures, or osteoporosis; furthermore, bone pain is present in 58 percent of the patients [[1](#_ENREF_1)]. Up to 90 percent of all patients will eventually suffer from bone destruction, which may result in pain, pathological fractures, nerve root compression, or hypercalcaemia [[2](#_ENREF_2)]. Because of this, patients with MM have a severely reduced quality of life (QoL) [[3](#_ENREF_3)]. Since Berenson *et al*. in 1996 demonstrated that the use of the bisphosphonate pamidronate can reduce the number of skeletal related events (SRE) and diminish pain, bisphosphonate has been the cornerstone in treating bone disease in MM [[4](#_ENREF_4)]. In 2003, the more potent bisphosphonate zoledronic acid was demonstrated to be “non-inferior” to pamidronate in reducing SRE in MM [[5](#_ENREF_5)]. Later it was demonstrated that zoledronic acid not only reduced the number of SRE but also increased overall survival with 5.5 months [[6](#_ENREF_6)], an association that had been very difficult to demonstrate for pamidronate [[7](#_ENREF_7)]. Likewise it has been demonstrated that patients without bone disease at diagnosis; evaluated with conventional radiography; may benefit from zoledronic acid. A significant reduction in the incidence of SRE has been observed in this subgroup of patients when zoledronic acid is initiated already at diagnosis [[8](#_ENREF_8)].

Duration of bisphosphonate treatment.

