Any radiological signs of bone disease including osteolysis (at least 10 mm), osteopenia, halisteresis, fractures including vertebral compression fractures (these findings are not necessarily equal to a Myeloma Defining Bone Disease Event; which is defined according to the International Myeloma Working Group Consensus Statement Paris 2011). No bone disease / Bone disease can be diagnosed on either conventional radiography or low-dose CT

QoL:

Quality of Life is evaluated using the European Organization for Research and Treatment of Cancer Quality of Life Questionnaire-Core 30 (EORTC QLQ-C30, version 3.0, together with the MY20 multiple myeloma specific supplement.

Primary Endpoint:

To compare the time to PBD from year 2 to year 4 in patients treated with monthly zoledronic acid in two consecutive years compared to patients treated with monthly zoledronic acid in four consecutive years.

Secondary Endpoints:

To compare the incidence of PBD from year 2 to year 4 in patients treated with monthly zoledronic acid in two consecutive years compared to patients treated with monthly zoledronic acid in four consecutive years.

To compare the incidence of sPBD from year 2 to year 4 in patients treated with monthly zoledronic acid in two consecutive years compared to patients treated with monthly zoledronic acid in four consecutive years.

To compare the incidence of bone healing from year 2 to year 4 in patients treated with monthly zoledronic acid in two consecutive years compared to patients treated with monthly zoledronic acid in four consecutive years.

To compare the overall survival from year 2 to year 4 in patients treated with monthly zoledronic acid in two consecutive years compared to patients treated with monthly zoledronic acid in four consecutive years.

To compare the incidence of BON from year 2 to year 4 in patients treated with monthly zoledronic acid in two consecutive years compared to patients treated with monthly zoledronic acid in four consecutive years.

To compare the development in QoL from year 2 to year 4 in patients treated with monthly zoledronic acid in two consecutive years compared to patients treated with monthly zoledronic acid in four consecutive years.

To compare the development in the bone markers CTX-I, PINP, bALP, and TRAP5b from year 2 to year 4 in the patients groups randomised to receive two or four years of treatment with zoledronic acid

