**1.9 Side Effects.**

Zoledronic acid has been approved by EMEA since 2001 for prevention of SRE in adult patients with advanced malignancies involving the bone. It has been used extensively for many years and has a well-known toxicity profile. It is not financially possible to conduct a new study where all possible side effects will be reported rigorous, as no pharmaceutical companies have shown interest in the study. Furthermore, it is unlikely that new – still unknown – side effects can be identified from this study since all patients most likely will receive multiple lines of anti-myeloma chemotherapeutics that will differ from site to site, and a significant portion of the patients will die due to progressive disease during the protocol. However, the Nordic Myeloma Study Group finds it very relevant to conduct a study with focus on BON, which is a late occurring, severely disabling side effect where the incidence increases proportionally to the exposure time. In this study, we will focus on BON and renal insufficiency as this is a common clinically relevant side effect to zoledronic acid. Patients will furthermore be evaluated using QoL, which ultimately will answer the question whether prolonged treatment with zoledronic acid is of benefit for these severely ill patients. All AEs and SAEs will be documented in the patient’s medical journal but will not be reported in the CRF if they can be related to the myeloma disease or to the chemotherapeutic treatment the patient receives. All SAR and SUSAR will be reported in the CRF. The treating physician decides if an AE or SAE is related to the investigational compound and thus should be reported as an SAR / SUSAR. Summary of Product Characteristics supplied in appendix 5 will be used as reference document to decide if a SAR should be upgraded to a SUSAR. All cases of renal insufficiency, BON, hypo-, and hypercalcaemia, will be reported in the CRF regardless of causality.

Registration of predefined (section 1.9.1 and 1.9.2) AEs, SAEs, SAR, and SUSARs will continue until the last infusions at year 4 +30 days for the treatment group or until year 4 +30 days for the observation group.

All national SAE, SAR, and SUSARs reported in the CRF during the trial will be listed and reported yearly by the national investigator to the National Health Authority and to the National Ethics Committee according to the national regulations by the national study secretary.

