**1.13 Statistical Considerations.**

Primary endpoint:

There are no published data on the incidence on PBD from year 2 and onward in MM. However, there are data showing the annual incidence of the more strict sPBD is approximately 5% in patients receiving continuous zoledronic acid [[31](#_ENREF_31)]. Since we in this study use a less strict definition of progression in bone disease, we assume the annual incidence will be 7.5% instead of only 5% in patients receiving zoledronic acid. Based on data from the MRC IX trial and from an ASH publication in 2012 we expect to see risk reduction rate of 0.5 [[32](#_ENREF_32)]. With a significance threshold of 0.05, one-sided, a power of 80, and a fixed study duration of 2 years, we need a sample size of 143 per group to detect a difference in the primary endpoint. 286 patients in total need to be allocated to the two treatment arms. However, due to the nature of the disease, 30% of all patients will be dead before year two. Due to the in- and exclusion criteria we presume that only 20% of the study population will be dead before stratification. Thus 358 patients in total need to be included in the protocol. Data will be analysed according to the treatment the patients actually received using the Kaplan-Meier analysis. Patients will be analysed per protocol. New data have shown significant reduction in PBD after 4 years treatment with zoledronic acid compared to 2 years of treatment in 170 randomised patients^33^.

Other endpoints:

Serum samples will be collected and stored from all patients. From the calculations above, we expect 32 cases of PBD during year two to four. Bone markers will be measured on these patients from the time of PBD and 6 month prior to the bone event. An equal number of controls will be selected as the number of cases PBD actually observed and bone markers will be measured likewise in these patients. The controls will be selected according the stratification criteria’s (previous autologous stem cell treatment, presence or absence of bone disease at diagnosis, and previous treatment with bortezomib). If multiple options are present the same gender will be chosen, and after that the closest age related. Data will be analyzed as a case control study

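### Kaplan-Meier is fixed for time to PBD with death outside the endpoint, so absolute PBD risks read from it will be somewhat too high; a cumulative incidence estimate with death as a competing event corrects this

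*Protocol*

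**What the plan says.** Protocol section 1.5 sets the primary endpoint: "To compare the time to PBD from year 2 to year 4 in patients treated with monthly zoledronic acid", two years against four. A secondary endpoint on the same event is a matter of absolute risk: "To compare the incidence of PBD from year 2 to year 4". The PBD definition in that section lists lesions, fractures and hypercalcaemia; death is not a component.

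Section 1.13, under the primary endpoint, fixes the method: "Data will be analysed according to the treatment the patients actually received using the Kaplan-Meier analysis". It names no test statistic and does not say how a death before PBD is handled. Section 1.12 lists death among the reasons for leaving the study and uses data up to the time of leaving.

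On mortality, section 1.9 states that "a significant portion of the patients will die due to progressive disease during the protocol". Section 1.13 expects 30% of all patients, and 20% of the study population, to die before year two. No figure is given for years 2-4. On a possible treatment effect on death, section 1.3 reports that "zoledronic acid not only reduced the number of SRE but also increased overall survival with 5.5 months".

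**The concern.** A patient who dies without PBD can no longer develop it. Kaplan-Meier with that patient censored estimates PBD risk as if the patient remained at risk, that is, in a population where nobody dies. One minus Kaplan-Meier is then at least as large as the proportion of patients who actually develop PBD, and strictly larger as soon as PBD occurs after some patients have died free of it.

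This matters because the trial's decision is a weighing of absolute risks. Section 1.14 asks whether protection against PBD justifies more osteonecrosis of the jaw (BON), and section 1.20 has the steering committee make the same weighing at the interim analysis. A PBD risk and risk difference read from Kaplan-Meier curves would enter that weighing too high.

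**Working it through.** **The plan's own figures first.** From section 1.13: "we assume the annual incidence will be 7.5% instead of only 5% in patients receiving zoledronic acid"; "we expect to see risk reduction rate of 0.5"; "With a significance threshold of 0.05, one-sided, a power of 80, and a fixed study duration of 2 years". Freedman's formula for a hazard ratio of 0.5 gives ((1+0.5)/(1-0.5))² × (1.645+0.842)² = 55.6, so 56 events. With rates of 0.15 and 0.075 per year, the two-year event probabilities are 1-exp(-0.30) = 25.9% and 1-exp(-0.15) = 13.9%. Then 56/(0.259+0.139) = 141 per arm against the stated 143. The inclusion target is 286/0.80 = 357.5, so 358. Both reproduce, and both allow for no deaths after randomisation.

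**Inputs for the check.**
- PBD: annual risks of 15% (arm A, stopped) and 7.5% (arm B, continued), so hazards λ = -ln(0.85) = 0.1625 and -ln(0.925) = 0.0780. This is the direction that reproduces 143.
- Death in years 2-4: **an assumption**. The upper values, 20% and 30%, are the protocol's pre-randomisation figures carried forward; 10% is a lower value. For two-year mortality d, the hazard is μ = -ln(1-d)/2, that is 0.053, 0.112 and 0.178. Mortality is taken as equal in both arms.

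**Formulas**, with constant hazards over two years:
- Kaplan-Meier with death censored: 1 - exp(-2λ)
- Cumulative incidence: λ/(λ+μ) × [1 - exp(-2(λ+μ))]

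Example, arm A at 20% mortality: exp(-2(λ+μ)) = 0.85² × 0.80 = 0.578, so the cumulative incidence is 0.1625/0.2741 × 0.422 = 25.0%, against 1 - 0.85² = 27.8% by Kaplan-Meier.

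| Two-year mortality | Arm A | Arm B | Difference (points) | Kaplan-Meier difference too large by |
|---|---|---|---|---|
| Kaplan-Meier, any | 27.8% | 14.4% | 13.3 | – |
| 10%, cumulative incidence | 26.4% | 13.7% | 12.7 | 0.6 points (5%) |
| 20%, cumulative incidence | 25.0% | 13.0% | 12.0 | 1.3 points (11%) |
| 30%, cumulative incidence | 23.6% | 12.2% | 11.4 | 1.9 points (17%) |

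**Rates instead of annual risks.** With λ = 0.15 and 0.075, the Kaplan-Meier difference is 12.0 points against 11.4, 10.8 and 10.2 at 10%, 20% and 30% mortality (5%, 11% and 17% too large).

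**The other reading of the PBD risks.** Section 1.13 also expects 32 PBD cases. That fits 7.5% v 3.75% per year: 143 × 0.15 + 143 × 0.075 = 32.2 over two years. The Kaplan-Meier difference is then 14.4% - 7.4% = 7.1 points (from unrounded values) against 6.7 at 10% mortality and 6.4 at 20%. The overstatement is about 0.35 and 0.7 points: about half as large in absolute terms, and similar in relative terms.

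**Unequal mortality, illustration only.** At 20% mortality in arm A and a death hazard ratio of 0.6 in arm B (assumed), arm B has μ = 0.0670. Its cumulative incidence is 0.0780/0.1450 × [1 - exp(-0.290)] = 13.5%, so the true difference is 25.0 - 13.5 = 11.5 points. Kaplan-Meier's 13.3 is then 16% too large. The overstatement of the difference disappears only if zoledronic acid roughly doubled the death hazard.

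**The case against.** The strongest case against has five parts.

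- **Wrong period.** The 20% and 30% are deaths before randomisation. Those randomised are survivors selected on renal function, absence of recent PBD and at least 12 infusions. This stands: mortality in years 2-4 is unknown, and at 10% the difference is off by only 0.6 points. Death is still not negligible on the protocol's terms: section 1.9 says so, and patients entering through the amendment need a life expectancy of only one year for a two-year follow-up.
- **Censoring is not written down.** True. It follows from an endpoint without death, analysed by Kaplan-Meier, with death ending follow-up. The sentence fixes the method, so a later analysis plan would have to depart from it.
- **Small against precision.** With 143 per arm, a simple binomial 95% interval on 27.8% v 14.4% is ±1.96 × √[(0.278×0.722 + 0.144×0.856)/143] = ±9.3 points. A shift of 0.6-1.9 points is modest beside that. This stands and limits the importance of the point, but the error is systematic and cheap to remove.
- **BON would be inflated too.** If BON were also read from Kaplan-Meier, its risk would rise by a similar factor and the ratio of PBD to BON would hardly move. But section 1.13 names no method for BON or sPBD incidence. A reader might infer that the plan puts these on Kaplan-Meier as well, or that the balance against BON is necessarily tilted; the text supports neither.
- **Mortality differing by arm is speculative.** A reader might infer from the 5.5-month survival gain that continuing zoledronic acid will change mortality in years 2-4. By its title in the reference list, the cited trial compared first-line zoledronic acid with clodronic acid; it does not address continuing beyond year two. Unequal mortality is therefore a scenario and not part of the stated size.

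**Conclusion.** The point holds within limits. Section 1.13 fixes an estimator that overstates the absolute PBD risk in each arm when deaths are censored, and overstates the risk difference if mortality is similar in both arms or lower on zoledronic acid. Assuming 10-30% mortality in years 2-4, equal in both arms, and annual PBD risks of 15% v 7.5%, the difference is 0.6-1.9 points too large (about 5-17% relative). Under 7.5% v 3.75% the absolute error is about half of that. These sizes rest on constant hazards and on a mortality range that the protocol does not give.

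A reader might infer that the primary comparison itself is invalid. It is not: a log-rank test or cause-specific Cox model that censors deaths validly compares the rate of PBD among patients still alive and free of PBD. The error lies in the reported risks and their difference. This is a worthwhile, inexpensive improvement and not a flaw that undermines the trial.

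**What to change.** In section 1.13:

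- Keep a cause-specific log-rank or Cox comparison of time to PBD as the primary test.
- Report the PBD risk in each arm, and the risk difference, by the cumulative incidence function (Aalen-Johansen) with death before PBD as a competing event.
- Add PBD-or-death as a sensitivity analysis.
- Use the same estimator for BON when it is weighed against PBD. No method is stated there now, so this is for consistency and does not correct existing text.

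Kaplan-Meier remains right for overall survival. The date and reason for leaving the study, including death, are already recorded under section 1.12, so no new data item is needed. The sample size calculation is not altered by this change. The cost is a sentence or two in 1.13, slightly more analysis work, and slightly lower reported incidences.

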Bone imaging should be conducted using both conventional radiography and low-dose CT. Sites however may participate in the study without conducting both conventional radiography and low-dose CT. In this case, the chosen modality must be used consistently throughout the entire study period.

Fasting serum bone markers should be collected every fourth week (+/- 1 week) throughout this period. Serum samples do not need to be collected at the exact date of zoledronic acid infusion but can be collected up to two weeks prior to infusion; serum samples however must not be collected after zoledronic acid infusion. Measurements of creatinine and calcium may be conducted up till 2 weeks before the visit

QoL questionnaire QLQ-C30 and MY20 will be used every 3^rd^ month: after 27, 30, 33, 36, 39, 42, 45, and after 48 months. All time-points can be moved -2 weeks.

Infusion with zoledronic acid in the treatment arm should be given ever 4^th^ week (+/- 1 week). Infusion can be delayed for up to 2 months e.g. due to temporarily impaired renal function (meaning a three month pause between two infusion is allowed). If infusions cannot be given within this time period the patient will be excluded from the study.

For specific instructions concerning conventional radiography and low-dose CT, see appendix 2

For specific instructions concerning serum bone makers, see appendix 3

Amendment:

Patients who are included after 23-25 zoledronic acid infusions outside protocol will move directly to randomisation. The randomisation procedure will be stratified according to previous autologous stem cell treatment, presence or absence of bone disease at diagnosis, and previous treatment with bortezomib. Randomisation will take place at The Hematological Research Unit, Odense University Hospital, Denmark. For further details see appendix 6 (SOP for randomisation).

Acquiring source data (amendment):

Bone imaging must not be done more than two months prior to inclusion and should be done no more than one month after inclusion.

Fasting serum bone markers must be collected no more that 2 weeks after inclusion.

QoL questionnaire QLQ-C30 and MY20 should be completed no more that 2 weeks after inclusion.

Investigation according to local guideline for any pre-existing BON must be conducted before inclusion in the protocol amendment

Planned visits, year 2-4: (amendment)

No changes compared to original description.

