**1.12 Withdrawal from the Study.**

In accordance with the current revision of the Declaration of Helsinki and applicable regulations, a

patient has the right to withdraw from the study at any time for any reason without prejudice to

his/her future medical care by the physician or at the institution.

Patients may be excluded from study in case of:

-significant protocol violation or non-compliance

-refusal of the patient to continue treatment and observations; withdrawal of consent

-if the investigator believes that for safety reasons (e.g., adverse events), it is in the best interest of the subject to stop treatment.

-if the patient due to renal failure is unable to receive zoledronic acid in two consecutive months (infusion can be delayed for up to three months). In case of tooth extraction, a delay of up to four months is allowed.

-if the patient due to BON stops treatment with zoledronic acid.

-if patients in the control arm experience progressive bone disease and the treating physician find it in the best interest of the patient to reinitiate treatment with zoledronic acid.

-if the subject becomes pregnant

-death

Patients excluded from the study will be followed for 30 days by the local hospital to insure registration of late occurring AE, SAE, SAR and SUSARs

The date and the reason for withdrawal status should be stated in the case report form. If the patient withdraws his or / her consent no further investigations will be conducted. If the patient is excluded for other reasons and it poses no risk for the patient fasting serum bone marker should be measured upon withdrawal, and bone imaging should be conducted no less than one month after withdrawal from the study. Data collected from the patient up until the time of withdrawal will if possible be used in the final evaluation of the study result unless the patient states it otherwise.

As stated in section 1.13, 286 patients need to be randomised to achieve enough power in the study. Patients will be included until this number is reached

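### The primary analysis is fixed by two different rules, neither of which compares all randomised patients by assigned arm, while removal rules before PBD differ by arm: bias of unsettled direction

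*Protocol*

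**What the plan says.** Section 1.13 (Primary endpoint) gives two analysis rules in consecutive sentences: "Data will be analysed according to the treatment the patients actually received using the Kaplan-Meier analysis. Patients will be analysed per protocol". No analysis by randomised arm appears anywhere in the protocol. The primary endpoint in section 1.5 also describes the groups by treatment given: "patients treated with monthly zoledronic acid in two consecutive years compared to patients treated with monthly zoledronic acid in four consecutive years".

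The removal rules after randomisation are these:

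- Infusion delay beyond the permitted gap, sections 1.7 and 1.8: "If infusions cannot be given within this time period the patient will be excluded from the study". Section 1.12 repeats this for renal failure.
- Osteonecrosis of the jaw (BON), section 1.12: "if the patient due to BON stops treatment with zoledronic acid". Section 1.8 says the same.
- Stopping arm only, sections 1.7 and 1.12: PBD has occurred and the physician decides to restart zoledronic acid.
- Either arm, section 1.12: "significant protocol violation or non-compliance", and also refusal or withdrawn consent, the investigator's safety decision, pregnancy and death.

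On what follows removal, section 1.6 plans no further protocol follow-up for patients who leave, early or on time. Section 1.12 keeps data up to withdrawal where possible, follows patients for 30 days for adverse events, and asks for one bone imaging after exclusion. It does not say whether PBD found on that imaging counts.

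**The concern.** Randomisation makes the two arms comparable only if all randomised patients are compared in the arm they were assigned to. A per-protocol set normally keeps the assigned labels but takes patients out. An as-treated analysis may move them to the other group. A patient in arm B (continue) who stops zoledronic acid early is handled differently under the two rules, and section 1.13 prescribes both.

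This matters here because removal is not symmetrical. After year 2 only arm B patients receive infusions, so the delay, renal and BON-stop rules can act only on them, and can act before PBD. The rule specific to arm A (stop) applies once the primary event has happened. Treatment-linked loss before the event therefore falls on one arm, for health-related reasons, in an open-label trial, and scheduled follow-up then ends. A result in either direction could partly reflect who was removed. This is more than detail left to an analysis plan: the protocol has made the choice, and a plan that follows it inherits both the choice and the conflict.

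**Working it through.** **1. The plan's own sample size.** Inputs from section 1.13: one-sided 0.05, power 80%, PBD 7.5% per year on zoledronic acid, two years. The stated risk reduction rate of 0.5 is read as a hazard ratio (HR) of 0.5, so 15% per year after stopping.

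- Events (Freedman): (1.645 + 0.842)² × [(1 + 0.5)/(1 − 0.5)]² = 6.18 × 9 = 55.6, so 56.
- Two-year event probabilities: 1 − exp(−0.15) = 0.139 and 1 − exp(−0.30) = 0.259.
- Per arm: 56/(0.139 + 0.259) = 141, against the stated 143.
- Total to include: 286/0.80 = 357.5, so 358, as stated.

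The figure reproduces. It has no allowance for removal after randomisation, so 143 per group is already the size for an analysis of all randomised patients with complete follow-up.

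**2. Which removals can precede PBD.**

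| Rule | Arm A (stop) | Arm B (continue) |
|---|---|---|
| Infusion delay, renal failure | cannot apply | can precede PBD |
| Stopping for BON | cannot apply | can precede PBD |
| Restart after PBD | only after the event | cannot apply |
| Non-compliance, consent, safety decision, pregnancy, death | possible | possible |

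**3. Size of the bias with no true effect.** The protocol gives no figure for removal after randomisation, so these inputs are assumptions: 143 per arm; PBD hazard averaging −ln(0.925) = 0.078 per year in both arms; 20% deaths over two years, hazard −ln(0.80)/2 = 0.112 per year; 10-20% of patients with 2-3 times the PBD hazard of the rest. In arm B these patients are removed at a uniform time over the two years if still alive and free of PBD. The test is a one-sided log-rank at 0.05. An HR below 1 favours continuing.

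| Handling of removed arm B patients | HR | One-sided error |
|---|---|---|
| As randomised, followed on | 1.0 | about 5% |
| Censored at removal | about 0.88-0.96 | about 6-10% |
| Dropped, or counted in the two-year group | about 0.96-1.12 | about 3-6% |

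The top of the last range (1.12) arises when patients are counted in the two-year group and nothing is observed after removal.

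**4. A second set of assumptions.** Here 25% of patients have three times the hazard of the rest, the average hazard is 0.15 per year in both arms, and arm B removal runs at 0.05-0.30 per year (about 7-40% removed before PBD).

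- Censored, removal unrelated to risk: HR about 1.0, error about 5%.
- Censored, removal 3-6 times likelier in high-risk patients: HR 0.99-0.90, error 5-11%.
- Censored, removal likelier in low-risk patients: HR 1.01-1.05, error 3-5%.
- Dropped: HR 1.02-1.44.
- Counted in the two-year group from randomisation: HR 1.03-1.78.

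The same null trial can thus lean either way, depending on a handling rule that section 1.13 leaves in conflict.

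**The case against.** A reader might infer that the plan is biased towards continuing zoledronic acid, with the error well above 5%. The documents do not support that. One-sided errors of 9-20% (dropped) or 12-38% (reassigned) appear only if every high-risk arm B patient is taken out from the start, whether or not PBD came first. The rules described would not remove a patient's earlier PBD event. Once only patients still free of PBD are removed, those figures disappear.

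An immortal-time argument is also tempting, because section 1.5 speaks of four consecutive years of treatment. Nothing in the protocol makes completing four years a condition of being counted in that group, and moving PBD-free patients to the two-year group adds event-free time there.

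Three further points stand:

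- Keeping data up to withdrawal (1.12) together with Kaplan-Meier (1.13) suggests censoring. There the error rises only to about 6-10%, and only if removed patients are at higher risk.
- That higher risk is not documented. Section 1.10 says that both myeloma and zoledronic acid can harm the kidney, and sections 1.3 and 1.4 tie BON to duration of exposure and dental procedures.
- Removal before PBD is not confined to arm B. The general reasons in 1.12 act in both arms, and an arm A patient who restarts zoledronic acid at relapse without PBD departs from 1.7 and could be removed as a violation.

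None of this supplies an analysis by assigned arm or reconciles the two rules.

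**Conclusion.** The point holds. The primary superiority analysis rests on two different rules, neither of which compares all randomised patients by assigned arm, and the treatment-linked removals that can precede PBD fall on one arm. The direction of bias is not established. Under the first set of assumptions the HR with no true effect runs from about 0.88 to 1.12 and the one-sided error from about 3% to 10%. Only censoring leans consistently towards continuation, and only if removed patients are at higher risk of PBD. If their risk is average, censoring gives no bias, but dropping or reassigning them still does. The removal fractions and relative hazards are assumptions, so the sizes are illustrative. The flaw itself is read directly from sections 1.13, 1.7, 1.8 and 1.12. It should be corrected, because it concerns the validity of the primary result and imaging not done after removal cannot be recovered later.

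**What to change.** - **Section 1.13:** replace both rules with one. The primary analysis takes all randomised patients in the arm assigned, from randomisation to PBD or year 4, regardless of later delay, stopping or restart of zoledronic acid.
- **Sections 1.7, 1.8 and 1.12:** separate stopping study treatment from leaving the study, so that scheduled imaging continues to PBD or year 4 unless consent is withdrawn. The rules on when treatment is delayed or stopped need not change for this.
- **Imaging interval:** section 1.7 schedules imaging half-yearly from year 2 to year 4, while section 1.8 says every three months. The two must be reconciled.
- **Per protocol:** keep it as a sensitivity analysis, with its membership and censoring rule stated.

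The sample size stays at 143 per group. The cost is wording, some dilution of the effect by non-adherence, and scheduled scans with their radiation in patients who stop. Section 1.14 does not treat that exposure as negligible. On the half-yearly schedule, though, these scans are among the seven already counted in section 1.8 for a patient who completes (45.5/7 = 6.5 mSv each with both modalities). Even without added scans, analysing by assigned arm with all available data would be worth doing.
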